### **5.2.4 Modified Directly Observed Therapy**

In this study, modified directly observed therapy (mDOT) will be used for both antituberculous and the punctuated ARV intervention. When medication is given by directly observed therapy, a health care provider, or designee, observes the patient swallow all pills and records that the dose was given. Directly observed therapy is an approach used to ensure adherence with study medication.

In this study, a team of home health visitors will deliver both the antituberculous and ARV treatment to study patients. The team of home visitors will be supervised by a single Ugandan medical officer. Home visitors will work with patients to determine a convenient time and place to deliver the medication Monday through Saturday. Home visitors will observe the patients swallow their pills six days a week. Thus, all antituberculous doses will be observed on these days and half of the punctuated ARV doses will be observed on these days because of the twice daily dosing. One day per week, patients will take their medication without medical supervision. Distribution of ARV medication will be strictly monitored to prevent misuse of study medication.

In the event that a patient defaults on a scheduled appointment with the home visitor, the home visitor will notify the study coordinator and begin to trace the patient.

The treatment supervisor will hold the patient’s anti-TB medications and treatment card. The patient and the treatment supervisor will both initial (or mark) the treatment card for each supervised dose63. The patient will initial (or mark) the treatment card for each unsupervised dose.

Before starting antiretroviral therapy, all patients will receive intensive counseling about antiretroviral therapy, especially ABC. They will be fully informed of the method of drug delivery through mDOT and will be counseled about the important of adherence with prescribed medication. They will be informed that unscheduled pill counts will be done to assess adherence to unsupervised doses.

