As part of the mDOT, patients will be given verbal and written material about the toxicities associated with each medication including ABC. The educational material will give specific information about ABC HSR. This information will describe the early signs and symptoms of HSR and the risk of continuing with ABC in the face of these symptoms. Patients will be instructed to contact the study personnel using the 24 hour per day telephone service or present to the clinic immediately. The patients will be told that a study doctor will make the decision to stop the medication, but it is their responsibility to notify the study doctors of the signs and symptoms of ABC HSR. Patients will be instructed that they may not take ABC at any time in the future if ABC HSR occurs. This counseling will be done by study personnel who are fully knowledgeable about the risks of antiretroviral therapy, especially ABC. All patients will be given a card that indicates that they are receiving ABC as part of this study. The card contains instruction for how to reach a study doctor. It will also instruct health care providers to notify study personnel regarding the health of the patient.

## 5.3 Post Outcome – Step 3

During the study period, patients in Step 2 may develop a primary study outcome. If this event happens, the outcome will be confirmed and patients will be evaluated for safety of starting antiretroviral therapy. Patients who have experienced the main study outcome and who are eligible to start antiretroviral therapy will enter Step 3. For patients with a primary outcome but not eligible for antiretroviral therapy, because of contraindications to starting ARV treatment, they will remain in Step 2 and have the safety assessments repeated monthly or as clinically indicated until they are found eligible for antiretroviral treatment.

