##### 6.3.1.2.1 Hypersensitivity Reaction (HSR) associated with Abacavir (ABC)

In clinical studies, approximately 3%-5% of patients receiving ABC develop an HSR that in rare cases has proved fatal. HSR is characterized by the appearance of symptoms indicating multi-organ/body system involvement. Symptoms usually appear within the first 6 weeks of starting treatment with ABC (median time to onset is 11 days), but may occur at any time while on therapy.

This section describes the diagnostic criteria that will be operationalized in the study. The clinical management of the syndrome is described under Clinical Management (Section 8.1.2.2.3). In this protocol we will distinguish the clinical diagnosis made at the time of evaluation from the final classification of a suspected HSR that will be used in the analysis. The clinical diagnosis will be made by the study team on-site using information available at the time of the evaluation. For the analysis, the Clinical Review Committee will examine all available data including the clinical course after ABC is withdrawn. This later classification will be used in the analysis of the study.

Clinical Diagnosis of ABC HSR

The diagnosis of HSR will be suspected when a patient receiving ABC presents to a routine or sick visit with a combination of fever, rash, gastrointestinal symptoms, worsening respiratory symptoms, neurologic symptoms. Although there is no diagnostic test available to confirm the clinical diagnosis of HSR, a routine medical evaluation will be performed including vital signs and physical examination looking for clinical characteristics of HSR. Standard laboratory evaluation will include CBC with differential count, serum chemistries, creatinine, and liver function tests. If liver enzymes are abnormal, then viral serologies for hepatitis A and B will be drawn.

Because the signs and symptoms of HSR are non-specific, and may be confused with side effects of rifampin, other HIV conditions, or paradoxical reactions, the evaluations of these patients will be as extensive as possible to allow for accurate diagnosis at the time of the event and proper classification for analysis.

HSR is defined as a clinical syndrome with findings from two or more of the following groups of signs or symptoms occurring simultaneously in a patient receiving ABC:

- Fever > 38°C
- Rash
- One or more gastrointestinal symptoms: nausea, vomiting, abdominal pain, diarrhea

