### **7.3.2 Intervention Phase Study Visit**

Following treatment assignment and initiation of study intervention, patients will be evaluated one and two weeks after initiation of ARV treatment and then monthly during study intervention phase (see Appendix I, Step 2).

1. Medical history and physical examination including weight, major TB and HIV-related signs and symptoms and primary study outcomes (Week, 2, Months 1, 2, 3, 4, 5, 6, and as indicated)
2. New diagnoses and/or hospitalizations since the last study visit (Week 2, Months 1, 2, 3, 4, 5, 6, and as indicated)
3. Posterior-anterior chest X-ray (8 weeks, and between 22 and 24 weeks)
4. Adverse experiences survey (Week 2, months 1, 2, 3, 4, 5, 6, and as indicated)
5. Sputum semi-quantitative AFB smear and culture on solid media X 2 (between 4 & 6 weeks, 8 weeks, and between weeks 18 & 20 from the start of anti-TB treatment)
6. MTB drug susceptibility (as clinically indicated)
7. Urine or serum -HCG pregnancy test (females of child bearing potential only) (Week 2, Months 1, 2, 3, 4, 5, 6, and as indicated)
8. CBC, differential white blood cell and platelet count (Week 2, Months 1, 2, 3, 6, and as indicated)
9. Serum aspartate aminotransferase (AST), serum total bilirubin (Week 2, Months 1, 2, 3, 6, and as indicated)
10. Serum creatinine (as clinically indicated)
11. CD4+ lymphocyte counts (Weeks 2, Months 1, 3, 6, and as clinically indicated)
12. Plasma HIV RNA by Roche Amplicor (Weeks 2, Months 3 and 6, and as clinically indicated)
13. Adherence Questionnaire for antituberculosis and antiretroviral therapy (Week 2, Months 1, 2, 3, 4, 5, 6, and as indicated)
14. Quality of life assessment (month 6)
15. Urine INH testing (Week 2, Months 1, 2, 3, 4, 5, 6)
16. Plasma storage (Weeks 1, 2, Months 1, 2, 3 and 6)
17. PBMC storage/ immune function (Week 2, Months 3, and 6)
18. Store MTB isolate for DNA fingerprinting (All isolates from positive cultures of suspected relapse cases will be stored at -70° C for DNA finger printing with the patient’s initial isolate, as clinically indicated)
19. Disease specific diagnostic test (as clinically indicated)

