4. Compare the results of CD4, HIV RNA viral load and anti-retroviral resistance testing from dried blood spot testing to those found using traditional venipuncture methods.

Patient population for virology sub-analyses:

Patients enrolled in the PART study at the TBRU in Kampala, Uganda will be included in these analyses. These patients are recruited from the National TB and Leprosy Program (NTLP) clinic in Kampala.

Analytic Design:

For this prospective nested sub-analysis of PART one additional blood draw will be scheduled to answer questions related to viral dynamics, viral subtypes, and anti-retroviral resistance. Additional virology and immunologic assays will be performed on banked serum and plasma specimens obtained during routine blood draws as outlined in the PART protocol.

In addition to the currently scheduled tests at baseline (HIV RNA and CD4 lymphocyte count), we will determine baseline HIV DNA, HIV genotype, HIV viral subtype, HIV co-receptor, presence of dual infection, and markers of immune activation (CD38+, DR+). We propose the addition of a plasma HIV RNA level at day 7 and day 14, and the addition of a CD4 lymphocyte count level at day 14 and day 28 (month 1) of the study intervention phase. At six months, testing to determine HIV subtype and presence of dual infection or recombinant variants, HIV DNA and RNA load, as well as antiretroviral resistance testing will be repeated in all patients. For patients randomized to receive immediate ART, repeat antiretroviral resistance testing will also be scheduled at the time of first positive VL specimen after discontinuation of ART at six months.

Viral decay after initiation and discontinuation of ARV will be analyzed assuming biphasic exponential decay characteristics. Comparisons of decay rates will be made using non-p

arametric methods (paired or unpaired Wilcoxon test). Clinical measurements of immune activation and viral RNA and DNA load, as well as baseline CD4+ lymphocyte count and markers of viral subtype and baseline resistance will be fitted in a multivariate regression model to determine independent predictors of first and second phase viral decay rates.

The presence of anti-retroviral resistance will be determined by standard sequencing methods. To determine independent predictors of resistance mutations, measurements of viral dynamics, including HIV RNA and DNA, and viral decay rates, as well as viral subtype will be analyzed in a multivariate model.

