Multi-region hybridization assay techniques will be used to quantify the presence of HIV viral subtypes, recombinant strains, and dual infection. Virologic and immunologic characteristics at baseline will be assessed to identify independent predictors of viral diversity.

Ethical considerations:

One additional study visit with one additional blood draw will be scheduled to accommodate the stated analytic goals. Patients may experience momentary discomfort during this additional blood draw. Adverse medical events are not anticipated. However, providers will manage untoward events or injuries according to routine practice. The virology sub-analyses does not require the collection of any additional, unique data, and will be conducted using information that has already been approved to be collected. The PART study informed consent has been amended to request permission from patients for one additional scheduled blood draw and clinic visit.

REFERENCES:

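### Section 7.3.2 speaks of an evaluation one week after antiretroviral start, but only plasma storage is scheduled then, so the first itemised examination and adverse event survey on abacavir is day 14, after the stated median hypersensitivity onset of day 11

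*Protocol*

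**What the plan says.** Section 7.3.2 opens by stating that "patients will be evaluated one and two weeks after initiation of ARV treatment and then monthly during study intervention phase" and refers the reader to Appendix I, Step 2. Of the 19 items that follow, one names week 1, item 16: "Plasma storage (Weeks 1, 2, Months 1, 2, 3 and 6". The AE item reads "Adverse experiences survey (Week 2, months 1, 2, 3, 4, 5, 6, and as indicated". History and examination (item 1), new diagnoses (item 2), blood count (item 8) and liver tests (item 9) also begin at week 2.

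The Step 2 grid agrees with the items. Its week 1 column has a single mark, in the plasma storage row, and a footnote to that row says viral dynamics. The rows for history and examination and for the AE survey are blank until week 2.

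The viral dynamics sub-analysis at the end of the protocol states: "We propose the addition of a plasma HIV RNA level at day 7 and day 14". Under its ethical considerations it adds: "One additional study visit with one additional blood draw will be scheduled to accommodate the stated analytic goals".

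On the hazard, sections 6.3.1.2.1 and 8.1.2.2.3 put HSR at 3 to 5% of patients on abacavir, usually within six weeks, with a median onset of 11 days and rare deaths. Section 8.1.2.2.3 adds that symptoms worsen if dosing continues.

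On contact between visits, section 5.2.4 says "Home visitors will observe the patients swallow their pills six days a week". On HSR it tells patients that "it is their responsibility to notify the study doctors of the signs and symptoms of ABC HSR".

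**The concern.** A site working from the item list and grid would draw blood at week 1 and examine nobody until day 14 unless a patient reported symptoms. Half of the expected HSR cases will have begun by day 11.

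Two statements elsewhere make the gap harder to read as intended. Section 6.3.1.2.1 says HSR will be suspected when a patient comes to a routine or a sick visit. With no clinical content at week 1, only the sick visit is left before day 14. Section 6.3.1 commits to finding serious events by active as well as passive means, but no active clinical assessment is itemised in those two weeks.

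Patient self-report is also under strain here. Section 6.3.1.2.1 gives the reason for working suspected cases up fully: "Because the signs and symptoms of HSR are non-specific, and may be confused with side effects of rifampin, other HIV conditions, or paradoxical reactions". Patients enter Step 2 two to four weeks into a rifampin-based regimen, so the first of those confusions applies to nearly all of them. At stake is delayed recognition of a reaction for which the remedy is to stop the drug promptly.

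**Working it through.** The protocol gives no figure of its own to reproduce. The check compares texts and then does simple arithmetic on stated rates.

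**1. Schedule.** The grid rows were read column by column. History and examination, AE survey, blood count, HIV RNA, plasma storage and PBMC each have 25 cells against 25 column headings, so the blank week 1 cells are not an alignment fault.

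| Assessment | Week 1 | Week 2 |
|---|---|---|
| History and examination | no | yes |
| AE survey | no | yes |
| Blood count | no | yes |
| HIV RNA | no | yes |
| Plasma storage | yes | yes |

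The first itemised clinical check is therefore at 2 × 7 = day 14, which is 14 − 11 = 3 days after the median onset. A check at day 7 would come 11 − 7 = 4 days before it.

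**2. Expected HSR cases.** Inputs: 175 patients in the punctuated arm (section 10.1) and 3 to 5% (section 6.3.1.2.1). This assumes that all 175 start abacavir.
- 175 × 0.03 = 5.25
- 175 × 0.05 = 8.75

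**3. Onsets before the first itemised check.** A median of 11 days means at least half begin by day 11, whatever the shape of the onset curve.
- 5.25 / 2 = 2.6
- 8.75 / 2 = 4.4

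**4. Ceiling on what a day 7 check can see.** Day 7 is before the median, so no more than half of onsets have occurred: at most 2.6 to 4.4 patients, fewer once those who have already reported are removed. The protocol gives no onset curve. As an illustration only, an exponential curve with median 11 days puts 1 − 2^(−7/11) = 36% of onsets by day 7 and 1 − 2^(−14/11) = 59% by day 14. That is 1.9 to 3.1 patients by day 7 and a further 1.2 to 2.0 between days 7 and 14.

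**5. Staff contact already planned.** Six observed days in seven gives 14 × 6/7 = 12 home visits in the first 14 days. Section 5.2.4 gives home visitors delivery, observation, recording and tracing of defaulters. It assigns them no symptom enquiry.

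**The case against.** The strongest reply is that nothing is contradicted. The protocol calls blood-only assessments evaluations elsewhere: section 5.2 says patients are evaluated at Step 2 entry and then lists only HIV RNA, plasma and PBMC, and section 7.3.1 does the same. The sentence in 7.3.2 defers to the grid, and list and grid agree. A day 7 draw for the sub-analysis fits a deliberate blood-only visit. This stands, so the wording is loose rather than firmly inconsistent. That week 1 entered the schedule through the sub-analysis is itself an inference.

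A reader might infer that there is no HSR surveillance before day 14. The documents do not support that. Section 5.2.1.1 requires a warning card, a review of HSR signs and the patient's own account of what to do, with physicians reachable at all hours. Section 7.5 allows a sick-visit work-up at any time, and items 1 and 4 of 7.3.2 allow extra checks when indicated. The manual of operations named in section 9.1 may also give home visitors duties not shown here.

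A reader might also turn step 3 into a risk. The chance of at least one onset by day 11 is at least 1 − 0.985^175 = 93% at 3% and 1 − 0.975^175 = 99% at 5%. That counts onsets. Nothing in the protocol allows an estimate of how many would go unreported or be stopped late.

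Nor should the case lean on paradoxical reactions. Their fever criterion in the IRIS definition (section 6.3) needs more than a week of fever after treatment starts, which day 7 cannot establish. Week 2 already lies inside the 1 to 3 week window of section 8.1.2.2.8.

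What the reply leaves open is that every safeguard before day 14, as written in this protocol, depends on the patient recognising and reporting symptoms or on someone deciding that an extra check is indicated.

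**Conclusion.** The point holds in a limited form. Section 7.3.2 leads the reader to expect an evaluation one week after antiretroviral start, while its items and the grid provide only a stored plasma sample. No itemised clinical check on abacavir takes place until three days after the protocol's own median HSR onset.

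About 5 to 9 HSR cases are expected, of which at least 2.6 to 4.4 begin by day 11. This rests on the stated 3 to 5%, the stated median and all 175 patients starting abacavir. It does not show that cases would be missed.

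The benefit of a week 1 check is confined to patients symptomatic by day 7 who have not already come forward. No primary outcome, analysis or stopping rule is affected. Severity is minor to moderate: a cheap safety improvement.

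**What to change.** In items 1 and 4 of section 7.3.2, and in the matching rows of the Appendix I Step 2 grid, mark week 1 for a brief history and examination and an AE survey that asks about the HSR symptom groups of section 6.3.1.2.1. The list and grid are not arm-specific, so the entry would apply to both arms and keep AE ascertainment even, in line with section 5.2.3.

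Optionally, for onsets between days 7 and 14, have home visitors ask the same short symptom list at the observed dose and call the study physician when two or more groups are positive, which is the protocol's own threshold for suspicion.

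The cost is a schedule amendment and a few minutes at a visit already planned, with no new visit and no extra blood. The optional step adds a short script to about 12 home visits per patient over the first two weeks if used throughout, or about 6 if confined to the second week (7 × 6/7).

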### **7.3.3 Post-Study Intervention Follow-up (prior to study outcome)**

Each subject will undergo the following examinations during follow‑up after completion of the six-month ARV Intervention Phase (see Appendix I, Step 2). After completing the intervention phase, patients will be seen monthly until month 12, and then patients will be evaluated every 3 months for a minimum of two years. A patient may be followed up to a maximum of five years depending on the date of enrollment; patients will be evaluated every 4 months after the first three years.

1. Medical history and physical examination including weight, major TB and HIV-related signs and symptoms and primary study outcomes (Months 7, 8, 9, 10, 11, 12, 15, 18, 21, 24, 27, 30, 33, 36 and *every 4 months thereafter or as clinically indicated*)
2. New diagnoses and/or hospitalizations since the last study visit (Months 7, 8, 9, 10, 11, 12, 15, 18, 21, 24, 27, 30, 33, 36 and *every 4 months thereafter or as clinically indicated*)
3. Posterior-anterior chest X-ray (Months 12, 18, and as clinically indicated)
4. Adverse experiences survey (Months 7, 8, 9, 10, 11, 12, 15, 18, 21, 24, 27, 30, 33, 36 and *every 4 months thereafter or as clinically indicated*)
5. Sputum semi-quantitative AFB smear and culture on solid media X 2 (Months 12 and 18, *or as clinically indicated*)
6. MTB drug susceptibility (as clinically indicated)
7. Urine or serum -HCG pregnancy test (as clinically indicated)
8. CBC differential white blood cell and platelet count (Months 9, 12, 15, 18, 21, 24, 27, 30, 33, 36 and *every 4 months thereafter or as clinically indicated)*
9. Serum aspartate aminotransferase (AST), serum total bilirubin (as clinically indicated)
10. Serum Creatinine (as clinically indicated)
11. CD4+ lymphocyte counts (Months 9, 12, 15, 18, 21, 24, 27, 30, 33, 36 and *every 4 months thereafter or as clinically indicated*)
12. Plasma HIV RNA by Roche Amplicor (Months 9, 12, 18, 24, 30, 36, and then annually or as clinically indicated)
13. Quality of life assessment (months 12, 18, 24, 30 and 36)
14. Plasma storage (Months 9, 12, 18, 24, 30, 36 and *every 4 months thereafter, or as clinically indicated*)
15. PBMC storage/ immune function (Months 9 and 12, *or as clinically indicated*)
16. Store MTB isolate for DNA fingerprinting (All isolates from positive cultures of suspected relapse cases will be stored at -70° C for DNA finger printing with the patient’s initial isolate, as clinically indicated)
17. Disease specific diagnostic test (as clinically indicated)

## 7.4 Measurements at Time of and Post- Primary Study Outcome

### **7.4.1 Time of Event (Primary Study Outcome)**

When primary study outcome is achieved, this will be confirmed with the following (section 5.3, appendix I, Step 3):

1. Medical history and physical examination, including weight
2. Adverse Event Survey
3. New diagnosis and hospitalization survey
4. Pregnancy test (urine or serum)
5. CD4+ lymphocyte count
6. CBC with differential
7. Liver function tests (AST and serum bilirubin)
8. Serum creatinine
9. Disease specific diagnostic test

These results will be valid for a period of two weeks and may be used for the safety evaluation, if within the acceptable range and time frame (2 weeks).

While the primary outcome is being confirmed patients will also be undergoing a pre-ARV safety assessment. If the evaluations below were not previously within the acceptable range or outside the two week time frame the evaluation that was not acceptable will be repeated. This ARV safety assessment may include results from the following (see Appendix I, Step 3):

1. Medical history and physical examination, including weight
2. Adverse Event Survey
3. New diagnosis and hospitalization survey
4. Pregnancy test (urine or serum)*
5. Complete blood count with differential
6. Liver function tests (AST and serum bilirubin)
7. Serum creatinine

Patients with contraindications to antiretroviral therapy at the time of the primary outcome will be re-evaluated in one month or as clinically indicated to determine whether contraindication to therapy has resolved. Laboratory assessments and physical exams will be valid for 2 weeks from the time of collection: after 2 weeks, tests will be repeated to assess contraindications to therapy (see section 5.3).

